### Intervention description {11a}

#### Intervention

DBED [10] is a 3-step method (Fig. 1) starting with both parents and kindergarten teachers completing the Early Worry Questionnaire (EWQ) (Step 1) as a preparation for the biannual parent-teacher conference. The EWQ contains 37 questions that systematically map possible concerns for the individual child’s wellbeing and development. When a concern is stated, the respondents are asked to suggest possible causes in an open-ended follow-up question. Step 2 is the parent-teacher conference where they compare their answers from the EWQ and discuss whether there is a reason for concern or not. In case of consensus of concern, a discussion of possible further actions should follow (Step 3), such as closer observation of the child, simple educational interventions (e.g., playgroup), or referral to more specific external assessment or services. During feasibility testing (*N* = 153) of the method, DBED was well accepted by parents and teachers [10]. Preparation before parent-teacher conferences by completing the EWQ facilitated a more active involvement of the parents in the dialogue. They also more often presented previously unspoken concerns for their child [10].

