The factor structure of EWQ as reported by parents and teacher, respectively, prior to the parent-teacher conference and as reported DBED concluded concern from the parent-teacher conference, primarily at baseline, but also at the following half-year registrations for comparative reasons.Agreement between (i) reported concern and DBED concluded concern, respectively, measured by total EWQ score and EWQ sub-scores, and (ii) mental health measured by SDQ Total difficulties score, each sub-scale score, and two SDQ impact scores, respectively, at baseline.Agreement between parent’s and teacher’s mental health report measured by agreement between parent and teacher SDQ scores and the above mentioned SDQ impact scores at baseline and after 12, 24, and 36 months, respectively.Agreement between parents and teacher in possible concerns for the child measured by percentage of EWQ items rated as the three different response options, respectively (satisfied; a bit uncertain; concerned), at baseline and after 12, 24, and 36 months, respectively).Change from reported to concluded concern during the parent-teacher conference measured similarly as the preceding outcome.Satisfaction with the DBED after all parent-teacher conferences measured by the study-specific satisfaction questionnaires for parents and teachers, respectively.Predictors of mental health change during the 5-year follow-up. Mental health is measured by SDQ-scores (Total difficulties score, sub-scales and impact scores) and the predictors (at baseline) are measured by:◦ Parent’s educational level◦ Satisfaction with economic situation◦ Social support◦ Single parenting◦ Close relatives in the vicinity◦ Norwegian language at home?◦ Is Norway parent’s country of origin?◦ Major illness or handicap◦ Level of parental concern◦ Level of teacher concern◦ Level of DBED concluded concern◦ Parent-teacher agreement after the parent-teacher conversation at baseline◦ Level of parental stressPredictors of parental and teacher concern, respectively. Concern is measured by parent and teacher EWQ total score at baseline and changes throughout the 3-year follow-up period in kindergarten, and the predictors are the same as for mental health change.Predictors of parental stress. Parental stress is measured at baseline and changes throughout the total follow-up period of 5 years, and the predictors are the same as for mental health change (except parental stress).Predictors of parent satisfaction. Parent satisfaction is measured by the study-specific satisfaction questionnaire at baseline and changes throughout the 3-year follow-up period in kindergarten, and the predictors are the same as for mental health change.

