### Recruitment {15}

By collaboration agreements, the three kindergarten organisations through their kindergarten managers have committed to facilitate recruitment of participants. Members of the project group have offered extensive information and training for teachers and parents in all kindergartens (see under the “ Strategies to improve adherence to interventions {11c}” section). A QR code linking to registration for potential participating parents is available in fliers and in the meetings with eligible parents. Consenting parents are offered two cinema tickets. During the recruitment period, the managers of every participating kindergarten are given feedback as to the consent rate in their own kindergarten compared to all the others’. Recruitment will continue every new kindergarten year (August to July) until consent is achieved from a minimum of 100 children in each arm.

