Baseline information (demographics, social support, health related information)◦ Parent’s educational level (values 0–3)◦ Satisfaction with economic situation (Visual analogue scale, values 0–10)◦ Social support, adapted from the PIRM study [15] containing nine items. See Additional file 2 for details.◦ Single parenting (values 0–1)◦ Close relatives in the vicinity (values 0–1)◦ Norwegian language at home? (values 0–1)◦ Is Norway parent’s country of origin? (values 0–1)◦ Major illness or handicap (child) (values 0–1)EWQ (only for the intervention group) [10] is a novel tool for assessing parents and kindergarten teachers’ possible concerns for a child. The psychometric properties of EWQ are not yet established but will be subject to analyses in the present study. We will apply the total EWQ score (values 0–74) and EWQ sub-scores (five sub-scores, values from 0–10 to 0–18). EWQ will be scored in two different situations:◦ Prior to the parent-teacher conference, completed by both each parent and teacher.◦ As conclusions after the parent-teacher conference, completed by teacherSDQ, 2–4 years version [16] is a standard screening tool for mental health symptoms among young children with well-established validity [16] and psychometric properties [17]. We will apply SDQ Total Difficulties Scale score (values 0–40), each sub-scale score (values 0–10), and two SDQ impact scores (values 0–3 and 0–12, respectively) addressing difficulties in general and in four different areas of daily functioning.PSS is an 18-item questionnaire (values 0–72) assessing parents’ feelings about their parenting role, exploring both positive aspects (e.g., emotional benefits, personal development) and negative aspects of parenthood (e.g., demands on resources, feelings of stress) [12].User satisfaction with the DBED method (only for the intervention group) measured after all parent-teacher conferences by study-specific questionnaires, see Additional file 2.◦ Parent questionnaire: five items (values 0–15) and optional free text response◦ Teacher questionnaire: seven items (values 0–21) and optional free text responsePossible supportive actions initiated, see Additional file 2.How specific questionnaires relate to the primary, secondary, and process outcomes, respectively, is described in the “Outcomes {12}” section. Collection of qualitative data for process outcomes is described in the “Data management {19}” section.

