## Statistical methods

### Statistical methods for primary and secondary outcomes {20a}

Primary outcome:◦ Possible differences between children in intervention and control kindergartens in mental health trajectories will be estimated by Latent growth curve (LGC) models (gives equal results as linear mixed/multilevel models, given similar parameter specification). Both random intercept fixed slope and random intercept random slope will be analyzed, meaning models with no variance in change (slope) and models with individual differences in slope (random effects). Then the full unstructured matrix with random intercept, random slope, and the covariance between intercept and slope will be tested. Initially, linear change over time will be tested. If not supported with data, different non-linear change models will be explored (quadratic, cubic, piecewise growth). Then, substantial predictors will be entered into the model and analyzed. Also, within level residual structures will be tested.Secondary outcomes:◦ Possible differences between children in intervention and control kindergartens in parental stress and time to initiated locally available supportive action, respectively, will be analyzed in a similar way to the primary outcome.Process measures:◦ Factor structure will be estimated by confirmatory factor analysis (CFA).◦ Agreements between:▪ Reported concern (EWQ) and DBED concluded concern (EWQ), respectively, and mental health (SDQ): correlations (Pearson’s and Spearman), Cohen’s (weighted) Kappa, CFA: uni-, bi-, and tri-factor models representing different sources of information (parent 1, parent 2, teacher. Latent difference score (LDS) models will also be explored for common levels and differences within and between families.Parent’s and teacher’s mental health report (SDQ): correlations (Pearson’s and Spearman), CFA, including method factors, LDS models.Parents’ and teacher’s possible worries for the child: Cross table with chi-quadrat test, Cohen’s weighted Kappa, CFA, and LDS models.▪ Change from reported (EWQ) to concluded concern (EWQ) during the parent-teacher conference: cross table with chi-quadrat test, Cohen’s weighted Kappa, CFA/LDS models.▪ Satisfaction with DBED:Initial: distribution of scores and mean values of each item. Mean value of total score.Follow-up: repeated measures of mean values of each item and total scores and LGC models.▪ Predictors of mental health change, parent concern, teacher concern, parent satisfaction, parental stress: LGC models with predictors (conditional LGC models).Statistical principles◦ Level of statistical significance: We will use the threshold of *p* = 0.05 for the main analysis. However, the threshold perspective has been debated, and there is considerable literature claiming another perspective as a relevant alternative. This implies the use of exact p-values as a degree of certainty of the generalization from sample to population. In the exploratory part of the project, this practice will be used. In addition, we will calculate effect sizes to evaluate the results beyond statistical significance.◦ Adjustment for multiplicity: Detailed power analysis (Monte Carlo analysis) was used to decide sample size for satisfactory power. Adjustment is irrelevant for this analysis. Regarding other statistical analyses, analyses may introduce risk for Type 1 errors when testing family-wise tests. When testing specific hypotheses (see above), no adjustment should be necessary. When exploring differences and relations not pre-specified in hypotheses (family wise tests), Bonferroni corrections will be used.◦ Confidence intervals to be reported: 95%◦ Methods used for assumptions to be checked for statistical methods: Residuals will be saved and checked for normality and homoscedasticity. Relations will be plotted and linearity in relations evaluated.◦ Details of alternative methods to be used if distributional assumptions do not hold: Bootstrapping will be used if normality does not hold. However, larger samples are robust for such deviations.If survival models (Cox and non-proportional parametric hazard models based on Weibull distribution), the proportional assumption will be tested. In addition, covariates will also be tested as time-dependent covariates to explore whether they relate to events differently over time.

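### Parent-teacher agreement on EWQ concern is measured over items but tested with chi-square and weighted kappa; if item ratings are pooled, as the text most naturally reads, p-values are too small and intervals too narrow

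*Protocol article*

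**What the plan says.** Outcomes {12} of the protocol article lists among the process outcomes "Agreement between parents and teacher in possible concerns for the child measured by percentage of EWQ items rated as the three different response options", at baseline and after 12, 24 and 36 months. The next outcome reuses the measure: "Change from reported to concluded concern during the parent-teacher conference measured similarly as the preceding outcome".

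Statistical methods {20a} gives the analysis of parents' and teacher's worries as "Cross table with chi-quadrat test, Cohen’s weighted Kappa, CFA, and LDS models". It names the same cross table, chi-square and weighted kappa, again with CFA/LDS models, for the reported-to-concluded change.

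The size of the questionnaire is in the Intervention section: "The EWQ contains 37 questions that systematically map possible concerns". Section {18a} restricts the EWQ to the intervention arm and says who fills it in before the conference: "Prior to the parent-teacher conference, completed by both each parent and teacher". Recruitment {15} continues "until consent is achieved from a minimum of 100 children in each arm", and Trial design {8} places the intervention arm in 10 kindergartens.

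**The concern.** A percentage of items in three ordered categories, set in a cross table with weighted kappa, has the item rating as its natural unit. The usual chi-square reference distribution and the large-sample standard error of kappa assume that every pair of ratings is independent. Here 37 pairs share one child, one parent and one teacher, and the children are grouped in 10 kindergartens.

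No safeguard in the article covers this. In {20a} bootstrapping is reserved for non-normality, and the assumption checks concern normality, equal variance and linearity. Bonferroni correction addresses the number of tests, not dependence within one. The multi-level adjustment in the Discussion concerns differences between the trial arms. Section {20a} also asks for 95% confidence intervals and, in the exploratory part, for exact p-values read as a degree of certainty. Both would overstate what about 100 children can show about how far parents and teachers agree, and about how concern moves during the conference.

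**Working it through.** **Inputs from the article.** 37 items with three response options; at least 100 intervention children; 10 intervention kindergartens; each parent and the teacher as raters; 95% confidence level.

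**Inputs assumed.** The article gives no correlation between items within a child and says that the psychometric properties of the EWQ are not yet established. I take a latent intraclass correlation (ICC) from 0 to 0.5 and a response split of 80/15/5%.

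**Step 1, reproduce the plan's own figure.** Scoring the three options 0, 1 and 2 gives a maximum of 37 × 2 = 74. This matches "We will apply the total EWQ score (values 0–74" and confirms 37 three-level items. No power or precision is stated for the agreement outcomes, so there is nothing further to reproduce.

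**Step 2, size of the pooled table.** 100 × 37 = 3,700 parent-teacher pairs, or 7,400 if both parents are used.

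**Step 3, percentages.** For the percentage of items in one category, the design effect is 1 + (37 − 1) × ICC, with the ICC on the scale of the category indicator.

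| ICC of indicator | Design effect | Correct CI width ÷ pooled width |
|---|---|---|
| 0.05 | 2.8 | 1.7 |
| 0.10 | 4.6 | 2.1 |
| 0.20 | 8.2 | 2.9 |
| 0.30 | 11.8 | 3.4 |

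At ICC 0.30 the 3,700 ratings carry the information of about 3,700 / 11.8 ≈ 314 independent ones.

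**Step 4, kappa and chi-square by simulation.** For each child and rater, the latent item rating is √ICC × (child effect for that rater) + √(1 − ICC) × (item residual), all standard normal, cut at the 80th and 95th percentiles. Each setting has 100 children, 37 items and 2,000 replications. In the related setting, parent and teacher effects and residuals each correlate 0.5, which gives a linear-weighted kappa of about 0.27. In the unrelated setting both correlations are 0.

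| Latent ICC | True SE ÷ usual SE of kappa (related) | Coverage of 95% CI (related) | Chi-square of association rejects (unrelated) | Chi-square of raters' percentages rejects (unrelated) | Same (related) |
|---|---|---|---|---|---|
| 0 | 1.02 | 94% | 4.9% | 4.4% | 2.5% |
| 0.1 | 1.05 | 93% | 5.6% | 22% | 11% |
| 0.2 | 1.20 | 89% | 7.3% | 35% | 20% |
| 0.3 | 1.49 | 81% | 12% | 45% | 30% |
| 0.5 | 2.23 | 62% | 33% | 61% | 49% |

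In every chi-square column the null hypothesis is true, so each rate should be about 5%. The ICC 0 row shows that the pooled methods do not over-reject, and cover close to nominally, when items really are independent. In kappa units, the usual 95% half-width is 1.96 × 0.0171 = 0.034. The true one is 1.96 × 0.0180 = 0.035 at ICC 0.1 and 1.96 × 0.0380 = 0.074 at ICC 0.5.

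Teacher and kindergarten clustering is not in this simulation and would add to the effect.

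**The case against.** The strongest reply is that nothing in the article says items are stacked across children. Outcomes {12} gives a measure and {20a} lists methods, and these need not meet in one table of 3,700 rows. Weighted kappa is also named for comparing the EWQ with the SDQ, whose items cannot be paired, so kappa in this plan does not by itself imply pooling. Item-by-item work appears elsewhere, for satisfaction. The variance formula for a process-outcome kappa is commonly left to the analysis plan. The same sentence also lists CFA and LDS models, in which the child or family is normally the unit. The correlation behind the size is assumed.

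Much of this stands. Pooling is an inference. If the tables are made item by item, each child contributes one pair per table and the within-child part disappears, leaving teacher and kindergarten clustering. The CFA and LDS models are not affected in the same way. At latent ICC 0.1 the effect on kappa is small.

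It does not remove the point. The article itself fixes both an item-percentage measure and the tests. Weighted kappa cannot be computed on one percentage per child without a categorisation that is not given, and 37 separate tables would not produce a percentage of items. Item counts by rater and response option is the reading that fits both sections.

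A reader might go further and infer that the protocol prescribes a naive pooled analysis, or that a central claim about DBED rests on it. The article supports neither: it states no pooling and no standard-error formula, and this is one of about ten process outcomes that the abstract does not single out.

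**Conclusion.** The point holds as a conditional one. Under the most natural reading, following the named tests would give p-values that are too small and confidence intervals that are too narrow for these two process outcomes. For kappa the understatement of the standard error runs from negligible (factor 1.05) to serious (2.2) over assumed latent ICC 0.1 to 0.5. For a chi-square comparing the raters' percentages, false rejection is 11% to 61% at a nominal 5% over the same range. The direction is the same at every positive ICC examined. The size rests on the assumed ICC, response split and parent-teacher correlation, none of which the article gives.

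It would be wrong to extend this to the growth-model comparison of the arms or to the secondary outcomes: none of them uses these tables.

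**What to change.** State the child as the unit for both outcomes. Either compute agreement per child across the 37 items, or compute weighted kappa per item across children and average over items. Take intervals and tests from a bootstrap that resamples whole children, or from a multilevel model with child and teacher or kindergarten effects. With only 10 kindergartens, a kindergarten-level bootstrap is itself unreliable and needs a small-cluster caution. Present any pooled item table descriptively, without a p-value. It would also help to say what the chi-square is for, since on a parent-by-teacher table it tests association rather than agreement.

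The cost is a few sentences in the analysis plan, a resampling or modelling step and wider intervals. No new data are needed.

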### Outcomes {12}

Primary outcome:

Effect of DBED on mental health measured as the difference between intervention group and control group in Total difficulties score of SDQ. Measurement scores will be recorded every sixth month during the entire 5-year project period (i.e., child-age 3 to 8 years) as repeated measures. SDQ sub-scores and two impact scores (difficulties in general and impact on four areas of daily functioning) will be analyzed. The primary endpoint will be during the last 3 months in kindergarten before the child starts school, giving total change over six time points of measurements. The secondary endpoint will be during the last 3 months in the second school year (10 time points of measurements).

Secondary outcomes:

Effect of DBED on time to initiated locally available supportive action analyzed as the difference in time (months) from inclusion to activation of such actions between the intervention group and control group as mean time (months) from inclusion to activation of such actions. This outcome will indicate if DBED may lead to earlier supportive actions for children.Effect of DBED on parental stress analyzed as the difference in total scores of the PSS between the intervention group and the control group [12]. Measurements will be recorded every sixth month during the project period. This outcome will indicate if DBED may lead to less or more parental stress and more or less self-confident parents.

Process outcomes:

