**Assessment**												
Baseline demographics and health information			x									
EWQ			x	x	x	x	x	x				
Conclusions DBED			x	x	x	x	x	x				
Actions^d^			x	x	x	x	x	x				
SDQ^e^			x	x	x	x	x	x	x	x	x	x
PSS			x	x	x	x	x	x	x	x	x	x
**Process evaluation**^f^												
Parent and teacher satisfaction^g^			x	x	x	x	x	x				
Interviews of parents and kindergarten teachers				x				x				
Audio recordings of parent-teacher conferences				x				x				

^a^Kindergarten year starts July 1^st^

^b^Informed consent is obtained a few weeks before intervention

^c^DBED and TAU are accomplished every 6 months

^d^Specified supportive actions within or outside the kindergarten, differentiated between old and new ones

^e^Data are collected 1 to 3 weeks after the intervention, but the scores relate to the child’s performance during the last 6 months

^f^Several of the questionnaires intended for primary and secondary outcomes, such as EWQ, Conclusions DBED, SDQ, and PSS, are also used in the process evaluation; see the “Outcomes {12}” section

^g^Includes also free text comments related to responder’s experiences of participating in the DBED method

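### Baseline concern and parental stress predict SDQ change in a growth curve that starts at the same wave, so shared error that fades after wave 1 can bias the coefficient towards improvement

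*Protocol article*

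**What the plan says.** Outcomes {12} of the protocol article lists "Predictors of mental health change during the 5-year follow-up. Mental health is measured by SDQ-scores". It then says that "the predictors (at baseline) are measured by" a list that includes parental concern, teacher concern, DBED-concluded concern and parental stress. Statistical methods {20a} gives the method as "LGC models with predictors (conditional LGC models", and for the primary-outcome growth models adds that "within level residual structures will be tested".

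The Participant timeline {13} puts the first EWQ, PSS and SDQ in one column (year 1, months 4–6). The SDQ footnote reads: "Data are collected 1 to 3 weeks after the intervention, but the scores relate to the child’s performance during the last 6 months". Outcomes {12} counts that wave as the first measurement: the primary endpoint is described as "giving total change over six time points of measurements" and the end of school year two as "10 time points of measurements".

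On raters, section {18a} has each parent and the teacher complete the EWQ before the conference, and the teacher record the concluded concern after it. The PSS concerns the parents' own feelings. Trial design {8} has the SDQ reported by both parent and teacher. The article does not say which SDQ report enters the predictor model. The EWQ is collected in the intervention arm only.

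**The concern.** A conditional growth curve treats the wave-1 SDQ residual as unrelated to the predictor. Here both are recorded within one wave, probably by the same person, about overlapping periods. A temporarily difficult spell, or a rater in a temporarily low mood, can raise EWQ, PSS and SDQ together. When SDQ later returns to its usual level, the model credits the return to the predictor's effect on the slope. This is regression to the mean.

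Two consequences follow. A concern or stress score with no real relation to change can appear to predict improvement, and a real worsening effect can be hidden. For the concern predictors there is no control-arm check, because controls have no EWQ; a spurious decline among children who caused concern could then be taken as a benefit of DBED. PSS is measured in both arms, so stress does not have that added problem.

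**Working it through.** The plan gives no figure for this analysis, so there is none to reproduce. The check asks how large the bias could be.

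**Inputs from the article.** SDQ SD 5.5, variance 30.25 (Sample size {14}); six waves to the primary endpoint and ten over five years (Outcomes {12}); about 100 children with EWQ data.

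**Assumptions not in the article.** The share *s* of SDQ variance that is occasion-specific (5% to 40%); the correlation *rho* between predictor and wave-1 SDQ residual (0 to 0.4); no true relation between predictor and change; shared error gone by wave 2 unless stated otherwise.

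**Why 5% as the low end.** In a simple growth-slope formula without slope variance, the variance of the arm difference in total change is (2/n) × 25 × residual variance / 17.5. With n = 100 per arm, 95% two-sided power for 0.8 points needs an SE of 0.8/3.605 = 0.222, hence a residual variance of about 1.7, which is 6% of 30.25. With n = 75 it is about 1.3, or 4%. The article does not state the residual variance, so this is only an indication.

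**Formula.** The least-squares slope gives wave 1 the weight (t1 − tbar)/Σ(t − tbar)². That is -2.5/17.5 = -0.143 for six waves and -4.5/82.5 = -0.0545 for ten. Multiplying by the number of intervals gives total change:

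- six waves: 5 × -0.143 = -0.714, so bias = -0.714 × rho × SD_resid
- ten waves: 9 × -0.0545 = -0.491, so bias = -0.491 × rho × SD_resid

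with SD_resid = 5.5 × √s. At s = 30%, SD_resid = 3.01; at 5%, 1.23.

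**Bias in total change per SD of predictor (SDQ points).**

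| s | rho | ten waves | six waves |
|---|---|---|---|
| 5% | 0.3 | -0.18 | -0.26 |
| 20% | 0.3 | -0.36 | -0.53 |
| 30% | 0.2 | -0.30 | -0.43 |
| 30% | 0.3 | -0.44 | -0.65 |
| 30% | 0.4 | -0.59 | -0.86 |
| 40% | 0.4 | -0.68 | -0.99 |

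Simulation with n = 100 agreed with the formula. Maximum-likelihood random-slope models at s = 30%, rho = 0.3 gave -0.49 (ten waves) and -0.66 (six).

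**False positives at p < 0.05, s = 30%, n = 100, no slope variance.** For rho 0.2/0.3/0.4: about 17/30/52% with ten waves and 21/44/67% with six. With a slope SD of 3 points and rho 0.3 these fall to 18% and 25%. Clustering and attrition were not modelled.

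**Masking.** If concern truly predicted worsening by +0.8, then at s = 30% and rho 0.3 the expected estimate is 0.8 − 0.44 = +0.36 over ten waves and 0.8 − 0.65 = +0.15 over six (simulated: +0.36 and +0.16).

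**How the error behaves over time.** If rho = 0 the bias is zero. If the shared error is the same at every wave, it goes into the intercept and the slope bias is again zero. If it decays gradually (autocorrelation 0.3 to 0.7, s = 30%, rho 0.3), the bias is -0.57 to -0.79 over ten waves and -0.73 to -0.81 over six.

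**Do the remedies work?** With error gone by wave 2 (s = 30%, rho 0.3), starting at wave 2 brings the bias to about zero and false positives to 5%. A direct path from predictor to wave-1 SDQ also leaves no bias beyond simulation noise. With gradual decay, part remains. At autocorrelation 0.5 over six waves, the five remaining waves give (-2×0.5 − 1×0.25 + 0×0.125 + 1×0.0625 + 2×0.03125)/10 = -0.1125. Then 5 × -0.1125 × 0.3 × 3.01 = -0.51, against -0.81 with all waves.

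**The case against.** The strongest reply is that the size depends on a transient correlation that the article does not report. A habitually gloomy rater is a lasting trait, which goes into the intercept. The SDQ looks back six months, which weakens the idea of one bad month. If the residual share is near 5%, the bias is small. All of this stands, and it is why the point says the bias can arise, not that it will.

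A reader might infer that the artefact is as large as the 0.8-point effect the trial was powered for. The documents do not support that. The analysis covers five years, hence ten waves, where none of the combinations examined with error gone by wave 2 reaches 0.8; at a 30% share only six waves with rho 0.4 does. The two figures also differ in kind: one is per SD of a predictor, the other a difference between arms.

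It can also be said that the false-positive rates are not the plan's decision rule, since {20a} ties the 0.05 threshold to the main analysis and uses exact p-values in its exploratory part. That is fair; the bias is the more relevant figure. Nor does the article say that an association between concern and slope would show that DBED works.

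Finally, the article says residual structures will be tested, and a conditional growth curve permits a path to wave 1. But a residual structure does not by itself free a correlation between the predictor and the wave-1 residual, and no such path is stated. The {20a} agreement analyses do allow for informant and method factors; the predictor models, as described, do not.

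**Conclusion.** The concern holds as a conditional one. The article fixes the predictors at baseline, fixes the model, and starts the curve at the same wave, with no stated safeguard. If predictor and wave-1 SDQ share error that fades, the coefficient is biased towards improvement by -0.30 to -0.59 points per SD over ten waves (-0.43 to -0.86 over six), assuming a 30% occasion-specific share and a correlation of 0.2 to 0.4. It is smaller at lower shares, and zero if shared error is absent or fully persistent.

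Three stronger readings are not supported. That the same respondent supplies both scores is likely but not fixed, because the SDQ informant is not named and concluded concern is entered after a joint discussion. A true worsening of 0.8 would be masked, not turned into apparent improvement, at the values worked through. And this is a process outcome: the randomised comparison of SDQ between arms is untouched.

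**What to change.** For the EWQ and PSS predictors of SDQ change, name the SDQ informant, keep the planned model, and add:

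- **(a)** a model with a direct path from the predictor to wave-1 SDQ, or one that starts the curve at wave 2;
- **(b)** a cross-informant model: teacher concern with parent-reported SDQ, and the reverse.

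If the result does not hold in these, describe concern or stress as predicting change only with caution. Treat the EWQ predictors of parental stress in the same way. Socio-demographic predictors can stay as planned.

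No new data are needed; the cost is wording and extra models. In (a) the slope SE widens by √(82.5/60) = 1.17, or 17%, with ten waves and by √(17.5/10) = 1.32, or 32%, with six. Starting at wave 2 also gives up the interval after the first conference, where a real early change might lie. Removal is incomplete if the error decays gradually. In (b) the informants are not fully independent, because the wave-1 SDQ follows a conference at which parent and teacher compared their answers. For these reasons both models belong beside the planned one as checks, not in its place or as a condition for any conclusion.
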